### Data management

Study data will be entered and stored in RedCap (Nashville, TN).

### Oversight

Cleveland Clinic’s Institutional Review Board (IRB) approved this study and considers it minimal risk. The National Institute on Aging (NIA) approved the protocol, members of an independent Data and Safety Monitoring Board (DSMB), and a DSMB charter. The IRB, NIA, and DSMB must approve protocol amendments and may specify terms for communication of amendments to trial participants.

## Discussion

PDP will be the first Phase III RCT to test the impact of an individualized decision tool to prioritize the delivery of nearly all major preventive services and closely rated chronic disease management services. Middle-aged patients are asked to adhere to up to 25 preventive service recommendations [43], a tall order for even the most motivated patients. Instead, they must prioritize based on factors including effort, available time, and acute medical needs, and even providers must prioritize discussion of evidence-based recommendations based on available time and perceived importance [11, 12, 16, 21]. PDP hypothesizes that patient outcomes will improve through a holistic understanding of which services are most likely to promote healthy aging, discussed with providers using shared decision-making.

This trial will expand prior literature in 3 dimensions. First, PDP will employ a mathematical model to translate evidence-based benefits and harms of preventive (and chronic disease management) services into a single metric, quality-adjusted life expectancy. Prior work focused on length, not quality, of life [20, 44, 45]. In prior work, both patients [21] and physicians [16] reported quality-of-life as a highly relevant metric by which to prioritize delivery of preventive services. Through this process, the resulting decision tool will offer a magnitude of benefit and rank-order, so that patients may better understand the relative importance of various recommendations.

Second, PDP will rigorously test a novel approach to decision aids, which seek to improve risk communication and shared decision-making [20, 46–48]. Whereas most tools consider single decisions; e.g., whether to take statins [49, 50], PDP will simultaneously address all evidence-based preventive services in an easy-to-follow 1-page bar graph [20]. Providers will be asked to spend their usual amount of time discussing preventive care, but reorganize the discussion holistically.

Third, model inputs will be obtained automatically from the EHR, alleviating the need for time-intensive manual data entry. This step should greatly improve the chances of reaching less motivated patients, who may be unwilling to complete a questionnaire with model inputs. This decision necessitates a provider-, rather than patient-facing tool in prior work [51], because EHR patient portals (which are accessed externally—outside a firewall) have less advanced capabilities than a clinician-facing EHR. We will do so in a generally scalable approach, which should facilitate eventual dissemination to other health systems, particularly those utilizing Epic^TM^’s EHR [52].

We note several limitations. First, even if the intervention increases QALE, there is potential for decrease in utilization of select preventive (or chronic disease management) services. For example, we may find that the intervention promotes tobacco cessation but reduces cancer screening utilization or vaccine uptake (because of lower expected benefits). Such a result would increase QALE—and therefore healthier aging, consistent with PDP’s objectives—but also result in some potential harm. Second, mathematical models are by nature imperfect. With DSMB approval, our model targets +/− 10–20% error compared with published population/policy-level models [53–60]. This is consistent with studies finding that patients better comprehend the gist (a central message, presented visually) than an exact magnitude [46, 61]. Third, the model’s recommendations will only be as good as EHR documentation quality. Previously, we developed and validated an EHR-based primary care registry of >800,000 primary care patients, giving confidence that overall documentation is excellent [62]. However, certain inputs (e.g., alcohol misuse, family history) are less-well documented [62]. Providers will be trained accordingly. Should the intervention prompt them to improve documentation, this limitation would become a strength.

In conclusion, the PDP cluster-randomized trial offers a rigorous design for evaluating the effect of individualized preventive service (and chronic disease management) recommendations on patient outcomes in routine primary care.

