
## Methods

The Personalized Disease Prevention (PDP) trial individualizes recommendations for preventive care and closely related chronic disease management services, based on 55 evidence-based risk factors. Each patient receives a different result based on his/her risk factors. Shown in a 1-page bar graph, patients may easily see which services are most likely to help them live a longer, healthier life. Providers may access the tool on-demand from the electronic health record (EHR) and are encouraged to discuss the individualized recommendations with patients using shared decision-making.

The foundation of the decision tool, called “individualized preventive care recommendations,” is a mathematical model developed by the study team. Previously published in proof-of-concept form [14, 15], the PDP model prioritizes 22 preventive and chronic disease management services based on their potential to improve a patient’s quality-adjusted life expectancy. Briefly, the model uses relative risk to adjust mean quality-of-life and survival probabilities (in 1-year increments) for the general population based on a patient’s age, sex, race, vitals, medical history, lifestyle, and family history. It then simulates the change in quality-of-life and survival probabilities achievable by following each preventive (or chronic disease management) service until the USPSTF-recommended stop age. For example, an individual who quits smoking would have lower risk of cardiovascular events, respiratory diseases, and various cancers, each of which would raise expected length and quality of life. Model parameters are derived from existing literature, often those referenced in evidence reviews or decision analyses accompanying USPSTF recommendations [14, 15]. It then rank-orders preventive services by the potential gain in quality-adjusted life years, to determine which services are most likely to help a patient live a longer, healthier life.

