^f^The USPSTF recommends weight loss counseling, which this RCT considers achievable through ≥1 of the following: bariatric surgery (assumed eligibility criteria: BMI≥40 kg/m^2^ or ≥35 kg/m^2^ in individuals with diabetes), healthy diet, and/or exercise. As with all services considered by the RCT, the individualized recommendations do not make a recommendation for or against receipt of bariatric surgery. The study assumes that a patient interested in bariatric surgery would have a discussion with his/her primary care provider and then a specialist. Additionally, the study team notes evolving evidence on medication (semaglutide) for weight loss, which may eventually be added to the RCT at the team’s discretion. The study team also may add a service Lose 10 lbs., intended to roughly proxy 5% weight loss, based on expected weight loss across available interventions (e.g., light exercise, partial adherence to healthy diet)

^g^Because the net benefit is likely to be small at the individual level (roughly, the public health benefit divided by the size of the at-risk population), the net benefit is assumed rather than mathematically modeled by the study team. For an average- or low-risk individual, typically assumed as ≤1 month of additional quality-adjusted life expectancy. Model documentation will provide further details, including definitions of high-risk factors and their individualized benefits (often, assumed as 1–2 months of additional quality-adjusted life expectancy)

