#### Providers

Through departmental staff meetings and direct invitations, the study team will contact eligible providers. Those who consent (via information sheet) will be randomized. Intervention arm providers will be invited to a 1-h training on the study, use of individualized preventive care recommendations and shared decision-making [36–39]. Those who complete the training will receive access to individualized preventive care recommendations in the EHR.

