### Collection of study endpoints

The primary outcome, change in patient QALE between the baseline encounter and 6 months later, and most secondary outcomes will be estimated through our mathematical model. Inputs will be obtained from an EHR data feed for each patient, from the baseline encounter through study completion. Select lifestyle endpoints with limited-no availability in the EHR (healthy diet, physical activity), wide variance in documentation quality (alcohol misuse) or that may have been changed since the last update in the EHR (tobacco) may be self-reported using validated scales in patient surveys [27–32]. The full study protocol specifies an objective algorithm in case EHR and self-reported data conflict.

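### Pre-existing family history, diagnoses or screenings charted after baseline can move the model-scored primary endpoint, mainly in the intervention arm

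*Protocol article*

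**What the plan says.** Under Collection of study endpoints, the protocol article states that the "change in patient QALE between the baseline encounter and 6 months later, and most secondary outcomes will be estimated through our mathematical model". On the source of the data it says: "Inputs will be obtained from an EHR data feed for each patient, from the baseline encounter through study completion". The opening of Methods lists medical history and family history among the model's inputs, beside vitals and lifestyle.

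The same endpoint section allows diet, physical activity, alcohol and tobacco to be self-reported on validated scales. It refers to an algorithm in the full protocol for conflicts between EHR and self-report.

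The limitations paragraph of the Discussion says that "certain inputs (e.g., alcohol misuse, family history) are less-well documented" and that providers will receive training to match, and continues: "Should the intervention prompt them to improve documentation, this limitation would become a strength". The statement on training names no arm. The only training described is in the Providers part of the Intervention section: "Intervention arm providers will be invited to a 1-h training on the study". No training of control providers is mentioned.

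On the model itself, Table 2, footnote f, says that a weight-loss medication "may eventually be added to the RCT". The notes to the same table tie eligibility for each service to the latest USPSTF recommendation.

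**The concern.** The endpoint is a calculation on what the chart contains, so a change in the chart counts as a change in the patient. Suppose a family history of cancer is first recorded two months after the baseline visit. The baseline score omits it and the 6-month score includes it, so the patient appears to lose QALE although nothing has happened. A screening done before baseline or elsewhere and entered later works the other way.

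If this happened equally in both arms it would largely cancel. Here the prompts to chart better (the training and the tool) belong to the intervention arm. Randomisation does not remove an artefact that the intervention itself produces. Nor does the mixed model's missing-at-random assumption, because the values are altered rather than missing. The arm difference would then mix real change with charting change, and a null result would be as hard to read as a positive one.

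**Working it through.** **Inputs from the article (Power).** 30 providers per arm, 10 patients each, ICC 0.01, target difference 3.0 months, power 86.2%. Sensitivity case: 54 providers, ICC 0.02, power 80.4%. The article gives no SD, significance level or sidedness, so a two-sided 0.05 level is assumed and the SD is back-solved.

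**Step 1: implied precision.**
- Design effect = 1 + (10 − 1) × 0.01 = 1.09. Effective n per arm = 300 / 1.09 = 275.2.
- 86.2% power requires 3.0 / SE = 1.960 + 1.089 = 3.049, so SE = 0.984 months.
- SD = SE / √(2 / 275.2) = 11.5 months.
- An observed difference above 1.96 × 0.984 = 1.93 months is significant.

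**Step 2: check against the plan's second figure.** With SD 11.54, 27 providers per arm and ICC 0.02: design effect 1.18, effective n = 270 / 1.18 = 228.8, SE = 1.079, power = Φ(3.0 / 1.079 − 1.96) = 79.4%, against 80.4% stated. A one-sided 0.05 level gives SD 12.9 and 80.2%. The two stated powers agree with each other to within about a point, so the implied SE is usable.

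**Step 3: effect of a charting artefact.** Let b be the net arm difference in change in QALE due to charting alone. The documents give no value, so a range is shown.
- False-positive rate with no true effect = 1 − Φ(1.96 − b/SE) + Φ(−1.96 − b/SE).
- Power if the artefact opposes a true 3-month effect = Φ((3 − b)/SE − 1.96).

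| Assumed b (months) | One way to reach it (net, intervention arm only) | False positives | Power if opposed |
|---|---|---|---|
| 0 | none | 5.0% | 86.2% |
| 0.3 | 10% of patients × 3 months | 6.1% | 78% |
| 0.5 | one sixth × 3 months | 8.0% | 72% |
| 1.0 | one third × 3 months | 17.4% | 53% |

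The 3-month unit follows the article's own scale: the Endpoints section values colorectal and breast cancer screening together at roughly 3 months.

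**Step 4: a model update between time points.** If an update shifts a share p of patients by s months equally in both arms, the expected bias is 0 and the SD becomes √(11.54² + p(1 − p)s²). With p = 0.5, s = 3 gives SD 11.64 and power 85.6%; s = 6 gives SD 11.92 and power 83.9%.

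**The case against.** **The sentence about a strength concerns the tool.** Its paragraph is about how far recommendations depend on EHR quality. A reader might infer that the article defends charting drift in the endpoint; it does not. What stands is that it welcomes better charting without noting the same data feed the primary outcome.

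**Lifestyle inputs have another route.** Alcohol, one of the two poorly documented inputs named, may be self-reported, Table 4 puts lifestyle measures in both patient surveys, and a conflict algorithm exists. It would be wrong to treat alcohol as unprotected. The protection is partial: the self-report wording is permissive, and the baseline survey follows the encounter at which the tool is discussed. Table 4 also collects self-reported service use, but only at 6 months. Family and medical history have no such route in the article.

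**Timing.** Training precedes tool access, so some prompted charting may already be in the baseline inputs. This shrinks the artefact but does not exclude later entries.

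**Model versions.** A reader might infer that mid-trial updates bias the result. The article does not say that the two time points use different versions, and the full protocol or model documentation may settle it. An added service need not alter a patient's scored QALE. Any update would apply to both arms, so Step 4 shows a small loss of precision and no expected bias.

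**Size.** A reader might posit shifts as large as 12 months per affected patient. In 10% of patients that would mean 1.2 months of bias, about 23% false positives or 45% power. Nothing in the article supports such a shift, and it sits high against the article's own scale, including the month or two assumed for the services in Table 2, footnote g. Artefacts of opposite sign would also partly cancel.

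**Conclusion.** The point holds for inputs without a self-report route in the endpoint section: family history, past medical history, and screenings done before baseline or elsewhere. For these, the feed as described lets a charting difference between arms enter the primary endpoint, in either direction.

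The size cannot be determined from the article. Across assumed net artefacts of 0.3 to 1.0 month the consequence runs from slight (about 6% false positives, 78% power if opposed) to serious (about 17% and 53%). The figures rest on a two-sided 0.05 level, the SE implied by the stated power, and an artefact that is net and confined to the intervention arm. The point also assumes that the training mentioned in the Discussion is the intervention-arm session, the only one described. It should be corrected because the remedy is cheap and the endpoint is the trial's primary one. The question of model versions is a minor matter of precision.

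**What to change.** For computing change in QALE in both arms:

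1. Hold non-modifiable inputs (family history, race) at the value recorded at baseline for both time points. An omission at baseline then stays an omission at 6 months and creates no change, and baseline does not depend on later charting.
2. Assign services by date performed and diagnoses by documented onset, not by date of entry.
3. Take lifestyle inputs from the patient surveys in both arms at both time points.
4. Add a sensitivity analysis restricted to measured or self-reported modifiable inputs.
5. Score both time points with one model version. The clinic-facing tool may still be updated.

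The cost is some programming and a few lines of analysis-plan wording, using the EHR feed and surveys already planned. There are two downsides. The analysed baseline QALE may differ from the figure shown at the visit. Some diagnoses will have an uncertain onset date, so item 2 reduces the problem for them without removing it; item 4 shows how much they matter.

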## Data Availability

De-identified participant data, subject to compliance with organizational policies; local institutional review board rules; local, state and federal laws and regulations, including the HIPAA Privacy Rule; and the NIH data sharing policy.
